#### Secondary outcomes

Clinical secondary outcomes are as follows: (1) “long-term efficacy”: number (percentage) of patients who reached a sustained 48-h grade 2, grade 1, or grade 0 classification on the WHO 8-point ordinal scale for clinical status assessment 10 days after starting treatment and within 28 days after hospital discharge; (2) time to achieve a clinical response: time (days) between visit 1 (treatment start visit) and the day of recording sustained 48-h grade 2, grade 1, or grade 0 classification on the WHO 8-point ordinal scale for clinical status assessment; (3) time to achieve an afebrile state: time (days) to reach a 48-h sustained afebrile state (i.e., body temperature ≤ 37.5 °C) without antipyretic medication; (4) time from symptom onset: time (days) between the first COVID-19-related symptom and visit 1 (treatment start visit); (5) number (percentage) of patients considered as responders based on National Early Warning Score 2 (NEWS 2)*. Responder is defined as a patient who reaches at least a sustained 24-h score ≤ 2; and (6) COVID-19-related relapse: number (and percentage) of patients discharged who presents a COVID-19-related relapse or comorbidity.

*Clinical severity assessment will be carried out using the NEWS 2: https://www.mdcalc.com/national-early-warning-score-news-2 [16]. This score, accessed by electronic devices, has demonstrated the ability to determine the degree of illness of a patient and prompts critical care intervention. The score is based on 7 clinical parameters (respiratory rate, oxygen saturation, any supplemental oxygen requirement, temperature, systolic blood pressure, heart rate, level of consciousness [Alert, Responsive to voice, Responsive to pain, Unresponsive]).

Safety secondary outcomes are as follows: (7) number (and percentage) of patients with any AEs; (8) number (and percentage) of AEs; (9) number (and percentage) of SAEs: according to their severity and relationship with treatment, and by determining the number of patients with a grade 3, grade 4, or grade 5 adverse event according to the CTCAE (Common Terminology Criteria for Adverse Events—see Table 2); (10) mortality for any cause: number (and percentage) of patients who died; (11) COVID-19-related mortality: number (and percentage) of patients who died due to COVID-19; (12) time until death: number of days from visit 1 until death; (13) COVID-19-related complications: number (and percentage) of patients who had any complications and number (and percentage) of complications up to 28 days after hospital discharge (visit 7); (14) number (and percentage) of patients who require intensive care; (15) number (and percentage) of patients requiring intensive care and invasive mechanical ventilation; (16) number (and percentage) of patients who require oxygen supplementation from hospital discharge up until visit 7; (17) number (and percentage) of patients diagnosed with another nosocomial infection; and (18) number (and percentage) of patients who requires hospital readmission within 28 (± 3) days from hospital discharge.

Safety assessment will be carried out from the treatment’s first dose up to 28 (±3) days after hospital discharge according to the CTCAE (all AEs, SAEs, and SUSARs will be reported in the e-CRF).

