#### Secondary objectives

The secondary objectives are as follows: (1) to study the time to achieve a sustained clinical response for 48 h, (2) to study the time to reach a sustained afebrile state for 48 h, (3) to study long-term efficacy 28 (± 3) days after hospital discharge, (4) to study the role of pharmacological treatments used in SoC in efficacy and safety, (5) to quantify hospital stay duration (in days), (6) to assess the influence of elapsed time from symptom onset (days with the disease) on treatment response, (7) to assess the incidence of COVID-19-related complications up to 28 (±3) days after hospital discharge, (8) to assess the incidence of SARS-CoV-2 pneumonia relapse from hospital discharge up until 28 (±3) days later, (9) to estimate the incidence of all-cause new emergency room visits from hospital discharge until 28 (±3) days later, (10) to estimate the incidence of mortality due to COVID-19 up to 28 (±3) days after hospital discharge, (11) to estimate the incidence of all-cause mortality through 28 (±3) days after hospital discharge, and (12) to estimate the incidence of adverse events (AEs) by severity up to 28 (±3) days after hospital discharge. To evaluate the safety of icatibant: incidence of adverse events by severity up to 28 (±3) days after hospital discharge.

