*Visits 2* and *3* will correspond to safety assessment during hospital admission. Visit 2 and visit 3 will take place, respectively, on day 2 (24 h after treatment start, before the 4th dose of icatibant) and on day 3 (48 h after treatment start, before the 7th dose of icatibant). *Visit 4* will take place 72 h after treatment start, end of treatment’ visit (after all doses are administered). Hospital discharge may occur after completing visit 4, if the patient is clinically stable (i.e., no fever for 48 consecutive hours without antipyretic medication, PaO_2_/FiO_2_ > 380 or O_2_ saturation > 94%, respiratory rate ≤ 24 bpm, absence of decompensation of any comorbidity).

*Visit 5* [10 (± 1) days after treatment start] will be an efficacy assessment visit. A clinical assessment will be performed and the patient’s clinical status and clinical stability criteria^#^, as well as the medication used and the presence of adverse events, will be reevaluated. If hospital discharge visit overlaps with the day 10 visit, the investigator will only complete the day 10 visit in the e-CRF, clarifying that it is also the hospital discharge visit. The patient will be sent home and will be informed of the confinement regimen measures to be followed at home (or similar, e.g., medicalized hotel), if necessary.

A patient classified as a treatment failure (i.e., non-responder—any patients who do not meet the criteria to be considered a responder) will have their participation in this study terminated. Afterwards, their condition will be treated at the discretion of the physician in charge of their particular case.

^#^Clinical stability (defined as (1) body temperature ≤ 37.5 °C for 48 h without any antipyretic medication, (2) PO_2_/FiO_2_ > 380 or oxygen saturation > 94%, (3) respiratory rate ≤ 24 rpm, and (4) the absence of any kind of comorbidity decompensation) will also be assessed and the time to achieve it will be calculated starting from the time of the baseline visit.

If the patient is discharged before the 10th day since treatment start, the investigator must complete the day 10 visit in the e-CRF for the efficacy assessment on the same day as hospital discharge.

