If the patient is discharged after the 10th day since treatment start, the date of hospital discharge will be recorded (*visit 6*). The following data will also be collected at the time of hospital discharge: the patient’s clinical status and clinical stability, the number of days on invasive mechanical ventilation (if required), the number of days on antiviral treatment (if administered), AEs, and SAEs.

The end of the study visit will be performed 28 days after hospital discharge. The patient will be informed that they will be called by phone on the 28th day after hospital discharge (*visit 7*) to assess the course of the disease. Patients will also be informed that they might be requested to report for a face-to-face appointment at the hospital, if considered necessary by the physician performing the phone interview. The aim of this visit is to collate potential relapses, readmissions, or new visits to the emergency room; information on complications related to COVID-19; number of deaths from any cause and cause of death (from hospital admission and up to 28 days after hospital discharge); and presence of AEs will also be collected.

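### Deaths, adverse events and COVID-19 complications are counted to 28 days after discharge, so each patient's observation time depends on length of stay, which is itself an outcome

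*Protocol article*

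**What the plan says.** All references are to the protocol article.

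- **Adverse events** (Secondary outcomes): "Safety assessment will be carried out from the treatment’s first dose up to 28 (±3) days after hospital discharge".
- **Complications** (Secondary outcomes): counted "up to 28 days after hospital discharge (visit 7").
- **Mortality** (Secondary objectives): "to estimate the incidence of all-cause mortality through 28 (±3) days after hospital discharge", and for the cause-specific version "to estimate the incidence of mortality due to COVID-19 up to 28 (±3) days after hospital discharge". The two mortality outcomes themselves name no window. Study procedure confirms it: deaths are collected "from hospital admission and up to 28 days after hospital discharge".
- **Last visit** (Study procedure): "The end of the study visit will be performed 28 days after hospital discharge". Table 3 times visits 1 to 5 in days from treatment start, but visit 7 in days from discharge.
- **Earliest discharge** (Study procedure): "Hospital discharge may occur after completing visit 4, if the patient is clinically stable". Visit 4 is at 72 h.

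Under Secondary outcomes, deaths, patients with adverse events and complications are summarised as counts and percentages. Statistical methods {20a} lists linear, logistic and Cox regression for the secondary outcomes without assigning a model to each. Duration of hospital stay is secondary objective 5. WHO grades 1 and 2, which count as response, are ambulatory states in Table 1.

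**The concern.** A percentage of patients with an event is comparable between arms only if both arms are watched for the same time. Here the window opens at treatment start or admission and closes at a point set by discharge. Discharge comes after randomisation, it is something the treatment is meant to bring forward, and in this open-label trial it is decided by physicians who know the allocation.

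An arm that leaves hospital earlier therefore has less time in which a death, adverse event or complication can be counted. A drug that shortens stay and does nothing else would look slightly safer. Simple percentages do not correct for this. Beyond the 10-day primary endpoint, the article gives no mortality, adverse event or complication comparison at a fixed day from randomisation.

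**Working it through.** The article derives no event rate, power or sample size (Sample size {14}), so it has no figure of its own to reproduce on this point.

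**Step 1. Window length.** Window from treatment start = stay + 28 days, or stay + 25 to stay + 31 with the ±3-day tolerance. Stay is counted here from treatment start.

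| Stay (days) | Window (days) | With ±3 days |
|---|---|---|
| 3 (earliest discharge, visit 4) | 31 | 28 to 34 |
| 7 | 35 | 32 to 38 |
| 10 | 38 | 35 to 41 |
| 14 | 42 | 39 to 45 |

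The 7 and 10 days are the ends of the range in which about 90% of such patients are expected to recover and go home (Concomitant treatment). Using them as the typical stays of the two arms is an assumption, and so is 14 days. For 7 versus 10 days, the observation ratio is 35/38 = 0.92.

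**Step 2. Constant hazard, no drug effect on the event.** With p the assumed 28-day risk, risk(t) = 1 − (1 − p)^(t/28). For p = 10%: 1 − 0.9^(35/28) = 12.3% and 1 − 0.9^(38/28) = 13.3%. The 95% half-width is 1.96 × √[r₁(1 − r₁)/60 + r₂(1 − r₂)/60].

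| Assumed 28-day risk | Stay 7 d | Stay 10 d | RR | Difference (points) | 95% half-width (points) |
|---|---|---|---|---|---|
| 5% | 6.2% | 6.7% | 0.92 | 0.5 | 8.8 |
| 10% | 12.3% | 13.3% | 0.93 | 1.0 | 12.0 |
| 20% | 24.3% | 26.1% | 0.93 | 1.8 | 15.5 |
| 30% | 36.0% | 38.4% | 0.94 | 2.4 | 17.3 |

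In 60 patients the difference is 60 × 0.005 = 0.3 to 60 × 0.024 = 1.4 patients. For stays of 7 versus 14 days, RR is 0.84 to 0.87 and the difference is 1.2 to 5.5 points.

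**Step 3. Falling hazard.** Events in acute COVID-19 may cluster early. Let the hazard halve every 7 or 14 days, with an assumed 28-day risk of 15%. The cumulative hazard is H(t) = −ln(0.85) × (1 − 2^(−t/h))/(1 − 2^(−28/h)), where h is the half-life, and risk = 1 − exp(−H).

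- h = 7 days: 15.5% (35 days) versus 15.6% (38 days), RR 0.99.
- h = 14 days: 16.3% versus 16.8%, RR 0.97.

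**Step 4. Common horizon.** If both arms are counted to the same day from visit 1, observation time is equal. A drug with no effect on the event then gives RR = 1.00, whatever it does to stay.

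**Step 5. Is day 28 reachable with the planned visits?** Earliest visit 7 = day 3 + (28 − 3) = day 28. Every patient followed as planned is therefore covered to day 28 from visit 1.

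**The case against.** The strongest reply is that the bias is small, concerns secondary outcomes, and is partly handled already. Much of this stands. The differences in Step 2 are well inside the confidence intervals, and the trial is a proof of concept with no superiority hypothesis. Time until death is counted from visit 1 and Cox regression is among the listed methods, so a censored analysis would deal with unequal follow-up for death. What remains is that the percentages of deaths, adverse events and complications are uncorrected, and that the error has a known direction.

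A reader might also infer more than the documents support:

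- **That emergency visits and readmissions have the same fault.** They do not. Their windows both start and end relative to discharge, so every patient discharged alive has 28 (±3) days whatever the stay.
- **That in-hospital deaths are lost.** Study procedure collects deaths from admission onward, so they are counted.
- **That the primary safety component is biased in this way.** As defined under Primary outcomes, it counts grade 3 to 5 events within 10 days of starting treatment and does not use the window ending at visit 7.
- **That observation times differ greatly between arms.** Single patients with extreme stays can differ widely, but with about 90% expected home within 7 to 10 days, the arms cannot plausibly differ on that scale.

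**Conclusion.** The point holds for mortality, adverse events (including serious ones) and COVID-19 complications, and for those only. Their observation time is stay plus 28 days, which depends on a post-randomisation event that the treatment is meant to change.

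If icatibant shortens stay from 10 to 7 days and has no effect on these events, the spurious relative risk is about 0.92 to 0.94 under a constant hazard and 0.97 to 0.99 under the falling hazards tried. These figures rest on assumed stays, event risks and hazard shapes, because the article gives no event rates. The effect is smaller than sampling error at 60 per arm, so it would not by itself decide the trial's conclusion. It is worth correcting because it is systematic, makes an arm with shorter stay look safer, and can be removed cheaply.

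**What to change.** Make the comparative analysis of mortality, adverse events/SAEs and COVID-19 complications cumulative to day 28 from visit 1 (randomisation), in all randomised patients, using event onset dates. Keep the counts to 28 days after discharge as descriptive.

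Two conditions apply:

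- **Onset dates.** The article implies a date of death, through time until death. It does not say that onset dates of adverse events and complications are recorded. Confirm that the e-CRF captures them, including for events reported at the visit 7 call.
- **Follow-up of non-responders.** Study procedure ends the participation of patients classed as treatment failures, while Secondary objectives, Secondary outcomes and the visit 7 description require follow-up to 28 days after discharge. These passages must be reconciled so that day-28 data exist for all patients. Otherwise follow-up would depend on response.

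Leave emergency visits and readmissions on their discharge-anchored window, as descriptive outcomes. Moving readmission to day 28 from randomisation without accounting for in-hospital time and death would create unequal time at risk: 28 − 3 = 25 days for a patient discharged on day 3, but 28 − 20 = 8 days for one discharged on day 20.

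The cost is a change of wording in the outcomes and analysis sections, with no added visit. The downside is that events after day 28 in long-stay patients leave the main comparison and appear only descriptively.

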### Trial design {8}

This study is a phase II, randomized, controlled, open-label, proof of concept, multicenter clinical trial with two parallel groups (experimental group: SoC-plus-Icatibant, and control group: SoC) to assess the efficacy and safety of icatibant in patients with COVID-19 pneumonia without invasive mechanical ventilation, and admitted to hospital units. The outcomes of the study protocol are based on the draft master protocol of the WHO for clinical trials that evaluate the efficacy and safety of investigational therapeutics for the treatment of COVID-19 in hospitalized patients (Table 1) [15].

**Table 1 Tab1:** WHO 8-point ordinal scale for clinical status assessment

Patient status	Score
Uninfected: No clinical or virological evidence of infection	**0**
Ambulatory, with no limitation of activities.	**1**
Ambulatory, with limitation of activities.	**2**
Hospitalized, not requiring supplemental oxygen	**3**
Hospitalized, requiring low-flow supplemental oxygen (mask or nasal prongs)	**4**
Hospitalized, on non-invasive ventilation or high-flow oxygen devices.	**5**
Hospitalized, intubated and mechanical ventilation.	**6**
Hospitalized, on invasive mechanical ventilation and additional organ support: extracorporeal membrane oxygenation (ECMO), renal replacement therapy, pressors.	**7**
Death	**8**

Patients enrolled in the study will be randomly assigned at a 1:1 ratio to the experimental group and the control group. The experimental treatment will consist of SoC-plus-Icatibant (3 doses per day for 3 consecutive days (a total of 9 doses). Each dose will consist of 30-mg icatibant administered subcutaneously. The control treatment will consist of SoC only.

Since the beginning of the COVID-19 pandemic, SoC has been mostly supportive, considering the lack of evidence for highly effective therapies. So SoC could vary depending on the scientific evidence available during the study. In this clinical trial (ICAT-COVID), SoC could include respiratory support measures, fluid therapy, antipyretic treatment, postural measures, low-molecular-weight-heparins, corticosteroids such as dexamethasone, remdesivir, and other therapeutic options.

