### Eligibility criteria {10}

*Inclusion criteria:*
Adult patients (≥ 18 years old), of both genders.SARS-CoV-2 infection confirmed by laboratory RT-PCR or antigen test ≤ 10 days prior to randomization.Hospitalized with a diagnosis of SARS-CoV-2 pneumonia.Radiographic evidence of pulmonary infiltrates of ≤ 48.Patients rated “4” or “5” on the WHO 8-point ordinal scale for clinical status assessment.PaO_2_/FiO_2_ < 380.Men and women of childbearing age who have heterosexual intercourse must agree to use safe contraceptive method(s).Subject or legally authorized representative must sign a written informed consent that states that he/she understands and agrees to comply with the planned study procedures.

*Exclusion criteria:*
Imminent death (life expectancy ≤ 24 h)Known hypersensitivity or known adverse reactions to the study drug, its metabolites, or excipients of the formulationInvasive mechanical ventilationParticipation in any other clinical trialALT or AST blood levels > 5 × ULN (upper limit of normal)Creatinine clearance < 50 mL/min using the Cockcroft-Gault formula for participants ≥ 18 years old [13]Patients with a recent acute coronary syndrome (< 1 month)Patients with cerebrovascular accident backgroundWomen who are pregnant or breastfeeding

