### Outcomes {12}

#### Primary outcomes

Primary outcomes are the efficacy and safety of icatibant: number (percentage) of patients considered as responders. Responder is defined as a patient who reaches a clinical response [sustained 48-h grade 2, grade 1, or grade 0 classification on the WHO 8-point ordinal scale for clinical status assessment (Table 1)] *and* who has not presented any severe adverse events (grades “3”, “4,” or “5” of the Common Terminology Criteria for Adverse Events -CTCAE- (Table 2)) within 10 days after starting treatment.

**Table 2 Tab2:** Common Terminology Criteria for Adverse Events (CTCAE) Version 4.0

Classification	Magnitude of the adverse event
**Grade 1**	Mild adverse event. Asymptomatic or mild clinical symptoms or just an observation; intervention not indicated.
**Grade 2**	Moderate adverse event. Minimal, local or non-invasive intervention indicated.
**Grade 3**	Serious or medically significant adverse event, but not immediately life-threatening. Hospitalization or hospitalization prolongation indicated; important limitation of self-care.
**Grade 4**	Adverse event with risk of mortality or disability.
**Grade 5**	Death associated with an adverse event.

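### The intensive-care and invasive-ventilation outcomes leave out patients who die before reaching either state, so a difference between arms on them can mislead or can hide harm

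*Protocol article*

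**What the plan says.** In Outcomes {12}, the secondary safety outcomes include item (14), the "number (and percentage) of patients who require intensive care", and item (15), the "number (and percentage) of patients requiring intensive care and invasive mechanical ventilation". Death belongs to neither. It is listed separately as item (10), "mortality for any cause: number (and percentage) of patients who died", item (11), deaths due to COVID-19, and item (12), "time until death: number of days from visit 1 until death". The article states no rule for a patient who dies before the event in (14) or (15).

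The primary outcome does take account of early death: a responder must reach the clinical response and be a patient "who has not presented any severe adverse events (grades “3”, “4,” or “5” of the Common Terminology Criteria for Adverse Events" within 10 days.

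Table 1 in Trial design {8}, the "WHO 8-point ordinal scale for clinical status assessment", already ranks the states concerned. Grade 6 is "Hospitalized, intubated and mechanical ventilation", grade 7 adds organ support, and grade 8 is death.

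Eligibility criteria {10} admit grades 4 and 5. On expected death they exclude only "Imminent death (life expectancy ≤ 24 h". Patients already on invasive ventilation are also excluded, as are those with certain renal, hepatic, cardiac and cerebrovascular conditions. No listed criterion concerns limits on intubation or intensive care.

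Statistical methods {20a} plans unadjusted and adjusted effect estimates with 95% confidence intervals for secondary outcomes, by linear, logistic or Cox regression. It names no composite with death and no method for competing events. Sample size {14} gives 60 patients per arm without a formal calculation and says that superiority is not the statistical hypothesis.

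**The concern.** Death without escalation prevents the event that (14) and (15) count. On the plain wording, a patient who dies on the ward adds nothing to either numerator, although that patient has reached the worst state on the trial's own scale. A lower ventilation rate in one arm could then mean fewer deteriorations, or the same number with more of them ending in death before intubation. The count cannot tell these apart.

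Such deaths are possible in grade 4 and 5 patients, and equal shares in the two arms cannot be taken for granted. The trial is open-label {17a}, rescue follows each hospital's own protocol (Rescue therapy, {11d}), and the participants' physicians collect the outcome data {18a}.

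Listing mortality beside these outcomes does not settle it. The marginal counts of ventilated patients and of deaths do not show how many patients had both, so the number with either cannot be recovered from them.

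**Working it through.** The protocol has no figure to reproduce here: it gives no rate for intensive care, ventilation or ward death, and no power calculation. The only input from the document is 60 patients per arm. All event counts below are assumptions.

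**Case 1: ward deaths replace intubation.** Let D patients deteriorate in each arm. In the control arm all D are intubated in intensive care. In the experimental arm w of the D die on the ward instead.

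- Outcome (15): (D − w)/60 v D/60, so RR = (D − w)/D.
- Ventilation or death: D/60 v D/60, so RR = 1.00.
- 95% CI: exp[ln RR ± 1.96 × SE], with SE = √(1/e − 1/60 + 1/c − 1/60), where e and c are the event counts in the two arms.

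For D = 6 and w = 3: e = 3, c = 6, SE = √(0.3333 + 0.1667 − 0.0333) = 0.683, RR = 0.50, CI 0.13 to 1.91. For w = 3 throughout:

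| D per arm | Outcome (15), experimental v control | RR (95% CI) | RR, ventilation or death |
|---|---|---|---|
| 6 | 3 v 6 (5.0% v 10.0%) | 0.50 (0.13 to 1.91) | 1.00 |
| 9 | 6 v 9 (10.0% v 15.0%) | 0.67 (0.25 to 1.76) | 1.00 |
| 12 | 9 v 12 (15.0% v 20.0%) | 0.75 (0.34 to 1.65) | 1.00 |
| 15 | 12 v 15 (20.0% v 25.0%) | 0.80 (0.41 to 1.56) | 1.00 |

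With a single such death (w = 1) the RR is 0.83, 0.89, 0.92 and 0.93 for the same four values of D. Each death that replaces an intubation lowers the arm's rate by 1/60 = 1.7 percentage points. The composite is imprecise too: at 6 v 6 its interval is 0.34 to 2.93.

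**Equal shares.** If shares sE and sC of the deteriorating patients die unventilated in the two arms, RR = (1 − sE)/(1 − sC). With sE = sC the ratio is 1.00, so the distortion needs an imbalance between arms.

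**Case 2: ward deaths are additional.** Take 9 ventilated patients in each arm and w extra ward deaths in the experimental arm. Outcome (15) is 9 v 9, RR 1.00. Ventilation or death is (9 + w)/9, which is 1.11, 1.33 and 1.67 for w = 1, 3 and 6.

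**Why separate counts do not suffice.** Suppose an arm reports 6 ventilated patients and 6 deaths. The number with either lies anywhere from 6 (all the same patients) to 6 + 6 = 12 (no overlap), that is 10% to 20% of 60.

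The same arithmetic applies to (14), with death before intensive care in place of death without intubation.

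**The case against.** Much can be said on the other side.

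- **The scoring is inferred.** The article gives no rule or denominator for patients who die, the word *require* could mean need rather than receipt, and an analysis plan that is not shown may settle this. That stands as a caution. What is fixed in the article is the outcome definition, and it leaves death out.
- **The two outcomes differ.** A patient who dies in intensive care without intubation is an event under (14). Only (15) misses every death without intubation.
- **The example is constructed.** The ratios come from an assumed imbalance of three patients, and every interval in the table includes 1. That stands: the calculation shows a mechanism and its possible size, not an expected result.
- **Death is visible elsewhere.** More ward deaths would show in items (10) and (12), and a death recorded as a grade 5 event within 10 days makes the patient a non-responder. This limits the harm. It does not repair (14) or (15): the primary outcome is binary, so a death and a patient still on oxygen in hospital at day 10 are both failures.

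A reader might infer that the arm with more ward deaths will always look better on these outcomes. The documents do not support that. It happens only if those deaths replace escalation, and more often in one arm than in the other. Additional deaths leave (15) unchanged. Nor do the documents support treating ventilation or death as the trial's main comparison of deterioration, because the protocol names no such comparison.

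**Conclusion.** The point holds in a limited form. Neither (14) nor (15) accounts for death as a competing event. If deaths without escalation replace it unequally between arms, the rates differ although deterioration is equal. If the deaths are additional, the rates agree although the arms differ in harm.

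Under the assumed 3 replacing deaths and 6 to 15 deteriorating patients per arm, the RR on (15) moves from 1.00 to between 0.50 and 0.80. These sizes rest entirely on assumed counts. The practical weight is modest: these are two of 18 secondary outcomes in a proof-of-concept trial that does not test superiority, and mortality is reported in its own right. This is a cheap improvement to the safety reporting. It does not call the primary result into question.

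**What to change.** In the secondary safety outcomes of Outcomes {12}, add two counts by arm:

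- number (percentage) of patients who reach WHO grade 6, 7 or 8, that is, invasive ventilation or death;
- number (percentage) of patients with intensive care or death.

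Use all randomized patients as the denominator and the same time window as (14) and (15). Keep (10), (14) and (15) as components, and say whether *require* means need or receipt. Neither new count has to be promoted to a main comparison.

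The data are already planned: clinical status daily in hospital and at each visit, days on invasive ventilation, and deaths to 28 days after discharge (Participant timeline {13} and Study procedure). Study procedure also ends participation for patients classed as non-responders. Any follow-up lost that way limits the new counts as it limits (10), (14) and (15).

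The cost is two more outcomes on a list of 18, each mixing events of different weight, which is why the components stay. Trial status reports 77 of 120 patients already enrolled, so the additions should be dated and described as made during recruitment.
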